# Efficacy and safety of artesunate for patients with IgA nephropathy: a study protocol for a multicenter, double-blind, randomized, placebo-controlled trial

**DOI:** 10.1186/s13063-022-06336-3

**Published:** 2022-05-25

**Keywords:** IgA nephropathy, Artesunate, Proteinuria

## Abstract

**Background:**

IgA nephropathy is the most common glomerular disease and is a common cause of progression to end-stage renal disease in patients with kidney diseases. Proteinuria levels are critical for the prognosis of patients with IgA nephropathy, but many patients are still unable to effectively control their proteinuria levels after receiving RAAS blockers. Antimalarial drugs have shown good efficacy in the treatment of kidney disease in previous studies; however, there have been no strictly designed randomized controlled trials to confirm the clinical efficacy of artesunate for treating IgA nephropathy patients. Therefore, we designed this clinical trial to compare the effect of artesunate versus placebo in patients with IgA nephropathy.

**Methods:**

This study is a randomized, double-blind, three-group-parallel, placebo-controlled clinical trial. One hundred and twenty eligible IgA nephropathy patients at risk of progression will be randomly divided into the artesunate 100-mg group, artesunate 50-mg group, and placebo group. Changes in proteinuria and renal function will be measured 6 months after the intervention. The levels of Gd-IgA1 and anti-Gd-IgA1 in the patient’s blood will also be tested to explore the possible immune mechanisms.

**Discussion:**

Clinical evidence supporting artesunate treatment of IgA nephropathy is currently lacking, and we expect that the results of this trial will provide high-quality clinical evidence for artesunate as a treatment option for IgA nephropathy in the future.

**Trial registration:**

Chinese Clinical Trial Registry ChiCTR2000038104. Registered on 10 September 2020

**Supplementary Information:**

The online version contains supplementary material available at 10.1186/s13063-022-06336-3.

## Background

Immunoglobulin A (IgA) nephropathy, characterized by prominent mesangial IgA deposition that is obfuscated on an immunofluorescence microscope, is the most common glomerular disease in the world [1]. The natural history of IgA nephropathy is highly heterogeneous; although the clinical data have shown that 50% of IgA nephropathy patients experience a sustained clinical remission, up to 40% of patients still develop end-stage renal disease (ESRD) within 20 years, and up to 40% experience a persistent decline in renal function [2–4]. The pathogenesis of IgA nephropathy is related to a “multi-hit” autoimmune process [5], which involves increased production of atypical galactose-deficient mucosal-type IgA1 antibodies, with the formation of anti-IgA1 autoantibodies, deposition of IgA1-containing immune complexes within the glomerular mesangium, and incitement of a nephritogenic inflammatory response by these immune complexes. Based on these underlying mechanisms, immunosuppressive drugs, including corticosteroids, are a potentially effective treatment option. However, the latest KDIGO Clinical Practice Guideline recommends that only patients who remain at high risk of progressive CKD (defined as proteinuria >0.75–1 g/day despite 90 days of optimized supportive care) should be considered for a 6-month course of glucocorticoid therapy, and the important risk of treatment-emergent toxicity must be discussed with patients (2B, moderate-quality evidence) [6]. This recommendation takes into account the current uncertainty over the safety and efficacy of existing immunosuppressive treatment choices [7] and the risk of serious adverse events (deaths related to infectious complications in the use of glucocorticoids [8], so for the patients who remain at high risk of progression in IgAN and eGFR ≥30 ml/min per 1.73 m^2^, the opportunity to take part in a clinical trial to search for safer and more effective alternatives to corticosteroids should be offered. Although the latest rituximab, eculizumab, and targeted-release budesonide may be potential treatments for IgA nephropathy, they are still far from being introduced into routine clinical practice because of their high cost and unclear risks of adverse events [9–11]. In the absence of more effective and available control therapies for IgA nephropathy with a high risk of progression, easier and safer supportive therapies are warranted.

Antimalarial drugs may provide a new treatment approach for the management of IgA nephropathy. In a recent randomized controlled study, IgA nephropathy patients with RAAS blockers received hydroxychloroquine (HCQ) for 6 months and had a nearly 50% reduction in proteinuria, which was significantly different from patients who received RAAS blockers without HCQ (a 10% increase) [12]. HCQ has also been reported to reduce the systemic lupus erythematosus disease activity index (SLE-DAI) and mortality in lupus nephritis and is currently the standard treatment for lupus nephritis [13]. The immunomodulatory and anti-inflammatory mechanisms of HCQ seem to interfere with lysosomal activity, inhibit antigen presentation and Toll-like receptor signaling at different levels, and thus affect T cell- and B cell-related immune inflammation, thereby reducing kidney injury and reducing proteinuria levels [14–16]. Importantly, these studies also identified fewer side effects with HCQ than with corticosteroids, which gives us more confidence that antimalarial drugs may be an effective management measure for IgA nephropathy.

Artesunate (ART) is a derivative of artemisinin (ARS), a component extracted from the traditional Chinese herb *Artemisia annua L.*, with improved pharmacological properties. ART has similar immunomodulatory effects to other antimalarial drugs [17], such as hydroxychloroquine (HCQ) and chloroquine (CQ), but has different active ingredients, which leads to the lack of risk of visual loss caused by HCQ [18]. Many experimental pieces of evidence have shown that ARS and its derivatives (ARSs) have good anti-inflammatory and immunomodulatory functions in SLE, rheumatoid arthritis, multiple sclerosis, inflammatory bowel disease, and other immune diseases [19]. ARS has been shown to improve podocyte injury, improve podoid fusion, and upregulate the expression of Nephrin and Podocin proteins in the podocytes of adriamycin nephropathy mice [20], and SM934 (an ARR) can reduce proteinuria, circulating antibodies, immune complex deposition in tissues, and podocyte injury and finally delay the progression of membranous nephropathy by inhibiting TGF-β1 expression and reducing the Smad2/3 expression pathway in Heymann nephritis mice [21]. More importantly, there is experimental evidence that ART combined with HCQ can effectively reduce 24-h urinary protein, IgA, and IgG immune complex deposition in the glomeruli of IgAN rats to reduce kidney damage through the NF-κB/NLRP3 signaling pathway [22]. Therefore, we hypothesized that ART might have the same excellent effects as HCQ in alleviating kidney injury and reducing proteinuria by inhibiting the activation and proliferation of B cells, inhibiting the generation of Gd-IgA1, and inhibiting inflammatory cytokines.

However, although a large amount of experimental evidence has been accumulated, there is still a lack of randomized controlled clinical trials to verify the potential effect of ART in the treatment of IgA nephropathy. This multicenter, double-blind, randomized, placebo-controlled study was designed to estimate the efficacy and safety of ART in IgA nephropathy. We present this protocol, which was prepared in accordance with the SPIRIT reporting checklist.

## Methods and design

### Study design

This study is designed as a double-blind, randomized, three-group-parallel, placebo-controlled superiority trial. One hundred and twenty patients with IgA nephropathy will be recruited, and the overall study design will be divided into two phases. In the pre-randomization phase, all participants will be confirmed to have received at least 3 months of RAAS blocker therapy to ensure that the patients have reached optimal blood pressure control (130/80 mmHg, the ideal range specified by the KDIGO2012 clinical practice guidelines) or have received the maximum tolerated dose of ACE inhibitor or ARB before entering the next phase. After qualification confirmation and informed consent, the enrolled patients will enter the post-randomization intervention phase. All participants will be randomly divided into the ART 100-mg group, ART 50-mg group, and placebo group for 6 months of intervention.

The flow diagram of the study process is shown in Fig. 1. Each participant will be assigned eight visits, including 3 months before the randomization (visit 1), 2 months before the randomization (visit 2), 1 month before the randomization (visit 3), randomization (visit 4), 1 month after the intervention (visit 5), 2 months after the intervention (visit 6), 3 months after the intervention (visit 7), and 6 months after the intervention (visit 8). The schedule for enrollment, intervention, and assessment is shown in Table 1. Retention of patients is promoted by close and frequent contact with their nutritional counselor and study physician via telephone, email, and study visits. In case of relevant issues, visits outside the study schedule are offered.

**Fig. 1 Fig1:**
[figure not shown]
The flow diagram of the study progress

**Table 1 Tab1:**
[figure not shown]
Schedule of recruitment, interventions, and assessments

^a^Items include urea, creatinine, total bilirubin, serum glutamic pyruvic transaminase, serum glutamic-oxaloacetic transaminase, alkaline phosphatase, sodium, potassium, calcium, phosphorus, total protein, albumin, and uric acid

^b^Items include urea, creatinine, sodium, and potassium

^c^Items include Gd-IgA1 and anti-Gd-IgA1(IgG/IgA)

*Abbreviation*: *HCG*, human chorionic gonadotropin

The primary outcome measures will be determined by the percentage change in proteinuria in the three groups after 6 months of intervention. The secondary outcome measures will be the changes in urinary protein creatinine ratio and estimated glomerular filtration rate (eGFR) from baseline after 1, 3, and 6 months of intervention, and the changes in serum galactose-deficient IgA1 (Gd-IgA1) and anti-Gd-IgA1 levels in patients will also be observed. We will stratify the risk of progression of the IgA patients and retrospectively evaluate the effect of ART on the proteinuria levels in IgA patients with different progression risks. Safety assessment of ART will be carried out throughout the study. The study protocol was approved by the Ethics Committee of Dongzhimen Hospital Affiliated with Beijing University of Chinese Medicine (Number: DZMEC-KY-2020-30) and registered in the Chinese Clinical Trial Registry (ChiCTR) (Number: ChiCTR2000038104).

This protocol has been reported according to the Standard Protocol Items: Recommendations for Interventional Trials (SPIRIT) 2013 statement [23]. The SPIRIT checklist is listed in Supplement Table 1. A complete list of clinic hospitals where data will be collected is available in Supplement Table 2.

### Participant recruitment

#### Inclusion criteria

The inclusion criteria for this study are (1) ages 18–75, (2) primary IgA nephropathy confirmed by renal biopsy, (3) persistent proteinuria ≥1.0 g/day after receiving adequate RAAS blocker treatment (proteinuria ≥1.0 g/day at visit 1 and visit 3), and (4) eGFR ≥30 ml/min per 1.73 m^2^ calculated by the Chronic Kidney Disease Epidemiology Collaboration (CKD-EPI) equation.

#### Exclusion criteria

The exclusion criteria included patients who had to be treated with corticosteroid immunotherapy (minimal-change disease with IgA deposition and the presence of crescents in more than 50% of the glomeruli on a renal biopsy within 12 months); patients who must be treated with other immunosuppressants (such as calcineurin inhibitors, cyclophosphamide, or mycophenolate mofetil); patients receiving systemic immunosuppressive therapy in the past 6 months; patients with uncontrolled hypertension (systolic blood pressure >160 mmHg or diastolic blood pressure >110 mmHg); secondary IgA nephropathy; acute kidney injury; malignant tumors; patients with serious diseases of other systems (such as liver damage, heart damage, diseases of the blood system, systemic infections, digestive ulcers); women who are planning to become or are pregnant; and patients with cognitive impairment who cannot sign the informed consent.

#### Withdrawal criteria

The subjects who no longer meet the inclusion criteria, have poor compliance, need immunosuppressive therapy, or have any other reason for violation of the protocol will be monitored by the investigators. These patients will be required to continue regular study visits as scheduled in the protocol after discontinuation of treatment. The data that need to be recorded is the end-point events and safety data that occurred during the duration of this trial.

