#### Termination criteria

Patients will be removed from the study if they develop severe liver or kidney damage during the trial (ALT or AST exceeding twice the normal upper limit, acute kidney injury), severe clinical discomfort caused by the drug (such as severe nausea and vomiting, severe dizziness, and headache), and severe drug allergies. All criteria and decisions will be jointly determined by two or more physicians with the title of deputy chief or higher.

Potential trial participants will be recruited from the six hospitals listed in Supplement Table 2. To reach the target sample size, the trial will be advertised in living communities by local healthcare professionals. We will also utilize advertising via brochures, flyers, or other means suggested through the clinic sites as appropriate. Before each interview, we described the aims of the study, guaranteed confidentiality, and obtained written informed consent. The interviews and examinations were achieved on the premises of the treatment hospital.

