### Outcome measurements

The primary outcome is defined as the percentage change of proteinuria in all three groups after 6 months of intervention. Secondary outcomes include the changes in urinary protein creatinine ratio (UPCR), eGFR, and serum Gd-IgA1 levels in all three groups from baseline. The clinical characteristics of the patients will be collected at baseline before enrollment, including age, sex, age, course of the disease, combined disease, medication history, and so on. Throughout the follow-up, patients will be asked to provide urine and blood samples, which will be collected independently at visit 4 and visit 8, which will be collected for the following: collection, storage, and distribution of biological samples and related data for scientific research in the biobank of Dongzhimen hospital. In order to assess drug compliance, participants will be checked for the remaining number of drugs at each follow-up visit. Patient compliance will be calculated as the percentage of the actually taken number of tablets (distributed pills − returned pills) to the distributed number of drugs.

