### Sample size

This is a double-blind, randomized, three-group-parallel, placebo-controlled clinical study, and the sample size estimates were based on the change in proteinuria levels. According to the study results when using similar types of drugs (HCQ) for the treatment of IgA nephropathy [12, 25], the average baseline proteinuria was 2.0±0.8 g/day, and 36 participants in each arm could provide 90% of the detection ability, assuming that the placebo group level of proteinuria had not changed, and the ART treatment detected a 25% reduction in proteinuria (ART group: 0.5±0.5 g/day). Assuming that the two doses of the ART group has the same efficacy (the ratio of the ART group to the placebo group is 2:1), and a 10% dropout rate with a type I error rate of 0.05, we plan to enroll 120 participants (40 in each group) in the study.

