### Statistical analysis

All results will be analyzed based on an intention-to-treat (ITT) analysis. Normally distributed data will be expressed as the mean ± standard deviation (SD), while nonnormally distributed data will be expressed as the median of the interquartile interval (IQR). Categorical data will be summarized as counts and percentages. The Shapiro-Wilk test will be performed to determine the normal distribution of continuous variables. For the comparison of baseline characteristics between groups, continuous variables (standard normal distribution) will be analyzed by a one-way ANOVA, continuous variables (nonstandard normal distribution) and ordered categorical variables will be tested by the Kruskal-Wallis *H* test, and unordered categorical variables or count variables will be tested by the chi-square test and Fisher’s exact test.

For the effectiveness outcomes, the primary outcome of proteinuria will be described by the percentage change of 24-h proteinuria test results at each visit from baseline, and the secondary outcomes of UPCR and eGFR will be described by the mean difference between the test results of each visit and the baseline. A paired-samples *t*-test or the Wilcoxon signed-rank test will be used for comparisons within groups at each visit time point from baseline, and one-factor ANOVA and the Kruskal-Wallis *H* test will be used for comparisons among groups at each visit time point.

For the safety indicators, adverse events will be described according to the number of cases and percentage, and the chi-square test and Fisher’s exact test will be used to analyze the differences between groups. The missing values will be filled up by the last-observation-carried-forward method. For the initial analysis, we will not adjust for confounders or stratification, and for the secondary analysis, we will adjust for confounders for subgroup analyses, such as baseline proteinuria (3 g/day), renal function (eGFR 45 m1/min per 1.73 m^2^), blood pressure level (systolic blood pressure 140 mmHg), MEST-C classification [26], and the new international risk-prediction score [27]. SAS 9.4 (SAS Institute Inc.) will be used as the statistical analysis tool. A 2-sided *P* < 0.05 will be defined as statistically significant.

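### The withdrawal clause on participants who cease to meet the inclusion criteria does not exempt proteinuria ≥1.0 g/day, so a site could read it as a reason to stop study drug in responders

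*Protocol article*

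**What the plan says.** Under Withdrawal criteria, the protocol article names its group as "The subjects who no longer meet the inclusion criteria, have poor compliance, need immunosuppressive therapy, or have any other reason for violation of the protocol". The verb attached to this group is mild: the investigators will monitor them. The next sentence requires the same participants to "continue regular study visits as scheduled in the protocol after discontinuation of treatment". No inclusion criterion is exempted.

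Inclusion criteria lists four conditions: age 18-75, biopsy-proven primary IgA nephropathy, persistent proteinuria ≥1.0 g/day on adequate RAAS blockade, and eGFR ≥30 ml/min per 1.73 m². The third is specified as "proteinuria ≥1.0 g/day at visit 1 and visit 3", and both visits fall before randomization.

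Outcome measurements states: "The primary outcome is defined as the percentage change of proteinuria in all three groups after 6 months of intervention". Statistical analysis adds that "the primary outcome of proteinuria will be described by the percentage change of 24-h proteinuria test results at each visit from baseline". Study design places three visits between randomization and the endpoint: "1 month after the intervention (visit 5), 2 months after the intervention (visit 6), 3 months after the intervention (visit 7", followed by visit 8 at month 6. Statistical analysis specifies ITT.

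**The concern.** Of the four inclusion criteria, biopsy-proven disease cannot lapse, and age lapses only for someone who passes 75 during the trial. In practice only proteinuria and eGFR can cease to be met after entry. A fall in eGFR below 30 is a plausible safety matter. A fall in proteinuria below 1.0 g/day is the response the trial is looking for.

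Proteinuria results are planned at each visit, so an investigator could see such a fall at months 1, 2 or 3 and, under the broad reading, stop the drug. That stopping would depend on the outcome and would be more frequent on ART than on placebo. ITT and continued visits would keep the month-6 value, but it would be measured off drug. Effect lost between stopping and month 6 cannot be recovered in the analysis. The likely direction is dilution toward no difference, not a false positive.

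**Working it through.** **Step 1: does the text reach responders?**

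| For the broad reading | Against it |
|---|---|
| The heading is Withdrawal criteria | The main verb says only that investigators monitor |
| The second sentence presupposes that treatment was discontinued | Criterion 3 is dated to visits 1 and 3, before randomization |
| Ceasing to meet a criterion describes change after entry | The list ends in protocol violations, and a response is not a violation |
| No criterion is exempted | eGFR <30 gives the wording a sensible post-entry use |

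The right-hand column makes the trigger uncertain. Nothing in it exempts a fall in proteinuria.

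**Step 2: how many participants could be affected?** The plan gives no figure to reproduce, so the sizes below are illustrative.

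Inputs from Sample size: baseline 2.0±0.8 g/day; placebo unchanged; "the ART treatment detected a 25% reduction in proteinuria (ART group: 0.5±0.5 g/day", taken as a fall of 0.5 with SD 0.5; 40 per group, hence 80 on ART. The mean response, 2.0 × 0.75 = 1.5 g/day, does not cross 1.0, so only the spread matters.

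Assumptions not in the document:
- The full 6-month planning effect is already present at months 1-3.
- The SD of change on placebo is also 0.5.
- Change is independent of baseline.
- Baseline B is ≥1.0 g/day and takes one of four shapes: (a) normal(2.0, 0.8) cut at 1; (b) log-normal with mean 2.0 and SD 0.8, cut at 1; (c) 1 + log-normal, matched to 2.0±0.8; (d) truncated normal on ≥1, matched to 2.0±0.8 (parent mean 0.378, SD 1.504).

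*Uniform 25% fall.* A participant is below 1.0 if 0.75B < 1, that is B < 1.333.
- Shape (a): [Φ((1.333−2)/0.8) − Φ((1−2)/0.8)] / [1 − Φ(−1.25)] = (0.2023 − 0.1056)/0.8944 = 0.108.
- Shape (b), log-mean 0.619 and log-SD 0.385: (0.1949 − 0.0541)/0.9459 = 0.149.

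If placebo is truly unchanged, its share is 0%.

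*Change of −0.5±0.5 on ART, 0±0.5 on placebo.* Given B, the chance of a value below 1.0 is Φ((1 − B + 0.5)/0.5) on ART and Φ((1 − B)/0.5) on placebo, averaged over B. For two low visits with independent changes, the probability is squared before averaging.

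| Share below 1.0 g/day | a | b | c | d |
|---|---|---|---|---|
| ART, uniform 25% fall, one visit | 0.108 | 0.149 | 0.113 | 0.227 |
| ART, −0.5±0.5, one visit | 0.222 | 0.281 | 0.303 | 0.326 |
| ART, −0.5±0.5, two visits | 0.112 | 0.148 | 0.149 | 0.191 |
| Placebo, 0±0.5, one visit | 0.075 | 0.099 | 0.098 | 0.127 |

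At one visit, ART shares therefore run from 0.108 × 80 = 8.6 to 0.326 × 80 = 26.1 participants. Placebo shares run from 0 to 0.127 × 40 = 5.1. If changes at the two visits were perfectly correlated, the two-visit share would equal the one-visit share.

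**Step 3: what effect would be lost?** This depends on how many sites read the clause broadly, when they stop drug and how fast the effect fades, none of which the document gives. Extreme cases show how wide the range is. Suppose every affected participant were stopped and the whole effect were gone by month 6.
- The uniform 25% fall would become 25% × (1 − 0.227) = 19.3% to 25% × (1 − 0.108) = 22.3%.
- The 0.5 g/day fall in the second model would become about 0.22-0.29 g/day.
- If only one of six equal-sized sites acted this way, the uniform fall would be 25% × (1 − 0.227/6) = 24.1% to 25% × (1 − 0.108/6) = 24.5%.

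These are not estimates. A fall first seen at visit 8 costs nothing.

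**The case against.** The strongest reply is that the document never orders responders off drug. Its verb is to monitor, criterion 3 describes two pre-randomization measurements that no later value can undo, and a trial built to measure response at 6 months would not sensibly stop responders. All of this stands, and it rules out saying that the protocol requires such stopping. It does not remove the ambiguity, because the same section is headed Withdrawal criteria, assumes treatment was discontinued and exempts nothing.

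A second reply is that senior review would catch a misreading: "All criteria and decisions will be jointly determined by two or more physicians with the title of deputy chief or higher". That sentence closes the run of criteria sections and may have been meant to cover them all. It stands, however, under Termination criteria, and it is not stated for withdrawal.

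Third, this is a journal article, and the full protocol may be narrower. That is possible, but the point concerns a rule the article states, not one it leaves out.

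Fourth, the numbers are generous. They place a 6-month effect at months 1-3, and most count a single low value although the criterion speaks of persistent proteinuria at two visits. Both criticisms are right. A site that waited for two low values would act on 11-19% of ART participants under the 0.5±0.5 model with independent changes. The shares show only that the clause could touch more than a handful of people.

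Finally, continued visits and ITT limit the harm. They preserve data and comparability, but not drug effect.

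**Conclusion.** The clause is too broad and should be narrowed. As worded, it can be read as a reason to stop study drug when proteinuria falls below 1.0 g/day, and that fall is movement on the primary outcome in the intended direction. Confidence is moderate, because the reading is possible and not compelled.

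If a site applied it, stopping would be outcome-dependent, more frequent on ART, and diluting. Under the assumptions in the working, chiefly that the full planning effect is present by months 1-3, about 11-33% of ART participants would be below the limit at one visit, against 0-13% on placebo.

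A reader might infer that responders will be withdrawn, or that the trial will lose a known part of its effect or power. The document supports neither: the trigger is uncertain, and the actual loss cannot be estimated from what is given. Nor does the point imply lost follow-up or a raised false-positive risk.

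**What to change.** In Withdrawal criteria, replace the general reference to the inclusion criteria with two specific grounds: ineligibility found to have existed at randomization, and named safety limits, for example an eGFR limit set by the clinicians. Add one sentence stating that a fall in proteinuria below 1.0 g/day after randomization is not a reason to stop study drug. Keep the continued visits and the ITT analysis as they are.

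The cost is one clause in the protocol and a note to the six sites. No visit, test or analysis changes.

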#### Dropout criteria

Patients who refuse to participate in the study visits for personal reasons or those whom the researchers are unable to contact through all available means will be regarded as dropouts.

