### Interventions

The intervention will consist of ART 100-mg group oral 50 mg ART tablets twice a day, ART 50-mg group oral 25 mg ART tablets twice a day, and placebo group oral equivalent placebo twice a day. The ART tablets and placebo will be provided by Guilin Nanyao Co., Ltd. All patients will receive standard support treatment for IgA nephropathy, including adequate RAAS blockers and blood pressure control. Permissible combination antihypertensive medications include diuretics, calcium channel blockers, and β-receptor blockers. Hydrochlorothiazide or loop diuretics could be used when antihypertensive targets are difficult to achieve. Statins and aspirins are also allowed when necessary. Prohibited drugs include proprietary Chinese drugs that may reduce proteinuria (such as *Tripterygium wilfordii*, *Penicillium notatum*, Huangkui capsules, nephritis rehabilitation tablets, Haikun Shenxi capsules), corticosteroids, and any immunosuppressants (such as mycophenolate mofetil, cyclophosphamide, azathioprine, HCQ).

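### The withdrawal criteria most naturally end randomised drug for poor compliance or any protocol violation, a small and avoidable source of bias towards no effect under intention-to-treat

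*Protocol article*

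**What the plan says.** The protocol article separates three situations under Participant recruitment.

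- *Withdrawal criteria.* The grounds are no longer meeting the inclusion criteria, together with subjects who "have poor compliance, need immunosuppressive therapy, or have any other reason for violation of the protocol will be monitored by the investigators". The next sentence reads: "These patients will be required to continue regular study visits as scheduled in the protocol after discontinuation of treatment". The data to be recorded for them are endpoint events and safety information.
- *Dropout criteria.* A dropout is defined by contact and not by drug intake: "Patients who refuse to participate in the study visits for personal reasons or those whom the researchers are unable to contact" through any available means.
- *Termination criteria.* This is the safety rule: "Patients will be removed from the study if they develop severe liver or kidney damage during the trial", with severe drug-related discomfort and severe allergy also listed. It adds that "All criteria and decisions will be jointly determined by two or more physicians" of senior grade.

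Other relevant provisions:

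- *Outcome measurements*: for compliance, "participants will be checked for the remaining number of drugs at each follow-up visit".
- *Study design*: visits 5, 6 and 7 fall at months 1, 2 and 3, and visit 8 at month 6, when the primary outcome is measured.
- *Interventions*: "Prohibited drugs include proprietary Chinese drugs that may reduce proteinuria", besides corticosteroids and immunosuppressants.
- *Statistical analysis*: intention-to-treat, with last observation carried forward (LOCF) for missing values.
- *Sample size*: 36 per arm for 90% power, raised to 40 for 10% dropout.

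**The concern.** Poor compliance and non-safety violations are things to record. They are not in themselves medical reasons to take a patient off drug. If the trial stops drug for them, it removes exposure that the patient might have kept, and intention-to-treat then counts that patient at full weight in the assigned arm.

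Two kinds of patient are affected. The first is the poor complier found by pill count at month 1, 2 or 3, who would have been off drug for 5, 4 or 3 months at the month-6 assessment. The second is the adherent patient who breaks another rule, for example by taking a prohibited proprietary product.

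At stake is a weaker estimate of the artesunate effect and some loss of power. The bias is towards zero, so it cannot create a false benefit. Keeping these patients in scheduled visits is right and should stay.

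**Working it through.** **Reading the text.** Safety stops sit under *Termination criteria* and loss of contact under *Dropout criteria*, so *Withdrawal criteria* must govern something else. Its second sentence refers back to the patients just listed and takes discontinuation of treatment as given. Ending randomised drug is therefore the natural reading. A weaker reading (if drug happens to be stopped, visits continue) is not excluded.

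**Inputs.** From *Sample size*: baseline 2.0 ± 0.8 g/day; 25% reduction, i.e. 0.25 × 2.0 = 0.5 g/day; SD 0.5 with artesunate; no change on placebo; type I error 0.05, two-sided per *Statistical analysis*. Assumed: placebo SD 0.8, equal to the baseline SD. Normal approximation throughout.

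**The plan's own figure.** At 1:1, n = (0.8² + 0.5²) × ((1.960 + 1.282)/0.5)² = 37.4, rounded up to 38, against the stated 36. Power at 36 vs 36: z = 0.5/√(0.89/36) = 3.180, and Φ(3.180 − 1.960) = 88.9%. This is close to the stated 90%. Dropout: 36/0.9 = 40, which uses the whole 10%.

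**Dilution model.** Let f be the fraction of artesunate patients stopped, with no effect left at month 6, and k the fraction of the effect they would have kept on drug.

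- Power if stopped: Φ(z(1 − f) − 1.960)
- Power if left on drug: Φ(z(1 − f(1 − k)) − 1.960)
- Loss caused by stopping: the difference between the two

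Poor compliers dilute the effect even if left on drug, so only this difference is avoidable. The documents give no f; 5% and 10% are assumptions (0.05 × 36 = 1.8 and 0.10 × 36 = 3.6, about 2 or 4 patients per arm).

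**From a nominal 90% design** (z = 1.960 + 1.282 = 3.242), power if stopped is 86.9% at f = 5% and 83.1% at f = 10%.

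| Effect kept if left on drug (k) | Power on drug, f = 5% / 10% | Loss from stopping, points |
|---|---|---|
| 0.25 | 87.7 / 85.1 | 0.8 / 2.0 |
| 0.5 | 88.5 / 86.9 | 1.6 / 3.8 |
| 1 (fully adherent) | 90.0 / 90.0 | 3.1 / 6.9 |

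**By comparison, with full loss of effect in those stopped:**

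| Comparison | z | f = 0 | f = 5% | f = 10% |
|---|---|---|---|---|
| 72 vs 36 (pooled 2:1) | 3.430 | 92.9% | 90.3% | 87.0% |
| 80 vs 40 (all 120 analysed) | 3.616 | 95.1% | 93.0% | 90.2% |
| 36 vs 36 (one dose vs placebo) | 3.180 | 88.9% | 85.6% | 81.6% |

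The 80 vs 40 row ignores dilution from dropouts whose values are carried forward.

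**Break-even for 90% power:** 1 − 3.242/3.430 = 5.5% stopped (72 vs 36); 1 − 3.242/3.616 = 10.3% (80 vs 40).

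**Sensitivity to the assumed placebo SD, 36 vs 36.** With SD 0.5 in both arms, power is 98.9%, and 96.8% at f = 10%. With SD 0.8 in both arms it is about 76% before anyone is stopped.

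**The case against.** The strongest objection is that the article never says drug is stopped for these reasons. Its verb is monitored, and a condensed article may leave stopping rules to the full protocol. This stands in part: the rule is inferred, and a reader should not claim that the plan orders discontinuation outright. But the point does not rest on a missing detail such as a compliance cut-off. It rests on printed text whose heading and second sentence point to discontinuation. The joint decision by physicians, even if it applied here, settles who decides and not on what grounds.

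A reader might also infer that the trial loses its 90% power because the dropout allowance leaves these patients out. The documents do not support that. The allowance is indeed for patients who leave follow-up, and withdrawn patients keep attending. But the sample size is framed on a pooled 2:1 ratio, which has slack under the assumed SDs. The one-dose comparison starts slightly below 90% before anyone is stopped, and its figure turns on a placebo SD that the article does not give.

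Three further points stand, and each makes the harm smaller:

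- If proteinuria is not among the data recorded after stopping, LOCF carries on-treatment values forward and dilutes less.
- The 3.1 and 6.9 point losses need fully adherent patients with no effect left. A patient stopped for taking a prohibited product that lowers proteinuria may still show a reduction at month 6.
- No scheduled visit falls between months 3 and 6. Non-compliance arising after visit 7 would be found by scheduled pill count only at visit 8, too late for stopping to affect the primary outcome.

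**Conclusion.** The point holds as a cheap improvement, with medium confidence. Read naturally, the withdrawal criteria end randomised drug for non-safety deviations, and under intention-to-treat this adds a small, avoidable bias towards no effect. Its size cannot be fixed from the documents. For poor compliers who would have kept a quarter to a half of the effect, it is about 1 to 4 power points at assumed stopping rates of 5% to 10%, given no residual effect at month 6. No failure of the stated power is shown: the pooled comparison holds 90% up to about 5.5% stopped, even with full loss of effect. That threshold depends on the assumed placebo SD of 0.8.

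**What to change.** Amend *Withdrawal criteria* to say that poor compliance and other violations without a safety reason are recorded as protocol deviations, and that these patients stay on assigned treatment and in scheduled visits. Study drug is stopped only for the reasons under *Termination criteria*, for other safety conditions such as pregnancy, for need of prohibited immunosuppression, or at the patient's request. The same sentence settles the wording if the weaker reading was intended.

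The cost is a wording amendment, with the IRB approval that *Protocol amendments and publications* requires for important modifications. It needs no extra visits, tests or patients. The downside is that more low-adherence patients stay on assigned drug and the deviation log grows longer.
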